### Data analysis

#### Sample size estimation

The sample size was based on showing a difference between groups for the primary outcome, success as defined by a Grade 1 on the Kindelan bone-fill index. Based on previous research (Paterson et al.), it is estimated that 60% of the treated will have a successful outcome. It is estimated that only 25% of the untreated group will have a successful outcome. With a 5% significance level and 80% power, it is calculated that 31 subjects per group, 62 in total are required for the study. To allow for a 10% non-compliance rate, 72 subjects will be recruited into the study.

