### Data analysis

Data will be analysed by an independent statistician. A detailed analysis will be planned before the final analysis of the trial. The main features of the statistical plan are mentioned here.

Data analysis will be carried out at the end of the study.

The primary outcome, Kindelan bone-fill index, is an ordinal measure and will be compared between groups using the Mann-Whitney test. Additionally, the outcome will be categorised as successful (grade 1) or unsuccessful (grades 2–4). The chi-square test will be used to compare the categorised outcome between groups.

Independent sample *t* test and 95% confidence intervals will be used for all continuous outcomes, for comparison between the groups. The dichotomous outcomes will be compared using chi-square test and the effect estimates will be reported using relative risk and 95% confidence interval. The qualitative outcomes will be compared using chi-square test.

A multivariable linear regression analysis will be carried out to assess the effect of pre-treatment complexity, gender and orthodontic treatment on the overall quality of alveolar bone graft success. The primary analysis will be on an intention-to-treat principle; the results of all subjects will be accounted for, regardless of the outcome of the treatment.

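### The only covariate-adjusted analysis is a linear regression with an unnamed response, and it fits neither the ordinal nor the binary form of the primary outcome

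*Protocol article*

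**What the plan says.** The Data analysis section of the protocol article, which lists the main features of the statistical plan, handles the primary outcome in two ways. First: "The primary outcome, Kindelan bone-fill index, is an ordinal measure and will be compared between groups using the Mann-Whitney test". Then the index is split into grade 1 (success) and grades 2 to 4 (failure), and "The chi-square test will be used to compare the categorised outcome between groups". For dichotomous outcomes in general, the section promises a relative risk with a 95% confidence interval.

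The one analysis with covariates comes next: "A multivariable linear regression analysis will be carried out to assess the effect of pre-treatment complexity, gender and orthodontic treatment" and the response is given as the effect "on the overall quality of alveolar bone graft success". No ordinal, logistic or relative-risk regression is named anywhere. The section adds that a detailed analysis will be planned before the final analysis.

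The Sample size estimation section sizes the trial on grade 1 success: "it is estimated that 60% of the treated will have a successful outcome", and "It is estimated that only 25% of the untreated group will have a successful outcome".

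**The concern.** The section calls the outcome ordinal and then names, for its only adjusted estimate, a model for a continuous response. It also does not say whether that response is the 1-4 grade or the grade 1 indicator. These are different analyses with different estimands:

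- **Response is the grade.** A step from 1 to 2 counts the same as a step from 3 to 4. The treatment coefficient is a difference in mean grade, which is not the quantity the trial was sized to detect.
- **Response is the grade 1 indicator.** The coefficient is an adjusted risk difference with ordinary constant-variance standard errors. It sits on a different scale from the relative risk promised for dichotomous outcomes.

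At stake is how the adjusted result can be read. It is the only estimate that accounts for pre-treatment complexity and for gender, the stratification factor in the Randomisation section. If it differs from the unadjusted success comparison, a reader cannot tell whether the cause is covariate imbalance or a change of scale.

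**Working it through.** **Inputs from the article.** Grade 1 success 60% (treated) and 25% (untreated), 5% significance, 80% power, 31 per group, 72 recruited, 1:1 allocation. I take the test as two-sided and use 72/2 = 36 per arm. Full four-grade distributions are assumptions, because the article gives only the grade 1 rates.

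**1. The plan's own figure.** With pooled p = (0.60 + 0.25)/2 = 0.425:

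n = [1.96 × √(2 × 0.425 × 0.575) + 0.8416 × √(0.60 × 0.40 + 0.25 × 0.75)]² / 0.35²
= (1.370 + 0.550)² / 0.1225 = 30.1, rounded up to 31 per group.

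This reproduces, and it confirms that the design quantity is the grade 1 success difference.

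**2. A one-directional benefit confined to grades 1 and 2.** Assume grades 1-4 at 60/15/15/10% (treated) and 25/50/15/10% (control). Cumulative proportions are 60/75/90 and 25/75/90, so no threshold worsens.

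- Mean grade, treated: 0.60 + 0.30 + 0.45 + 0.40 = 1.75. Control: 0.25 + 1.00 + 0.45 + 0.40 = 2.10. Difference 0.35.
- Variance, treated: 4.15 − 1.75² = 1.0875. Control: 5.20 − 2.10² = 0.79.
- Standard error at 36 per arm: √[(1.0875 + 0.79)/36] = 0.228. Ratio: 0.35/0.228 = 1.53.
- Approximate power: Φ(1.53 − 1.96) = 0.33.

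Simulation, using the two-group linear model without covariates, agrees: about 33% for linear on grade, 54% for Mann-Whitney and 87% for chi-square on grade 1. Linear regression on the 0/1 outcome has about 85%.

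**3. A proportional-odds shift with the same success rates.** The odds ratio is (0.60/0.40)/(0.25/0.75) = 4.5. Applied to control 25/50/15/10%, it gives treated 60.0/33.1/4.5/2.4%, with mean 1.49 against 2.10. Across three assumed control distributions (25/25/25/25, 25/40/20/15 and 25/50/15/10):

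| Per arm | Linear on grade | Mann-Whitney | Chi-square on grade 1 |
|---|---|---|---|
| 31 | 84-87% | 87-88% | 82-83% |
| 36 | about 89-92% | 91-93% | 86-87% |

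**4. The extreme case.** Assume treated 50/10/10/30% and control 25/40/25/10%.

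- Mean, treated: 0.50 + 0.20 + 0.30 + 1.20 = 2.2. Control: 0.25 + 0.80 + 0.75 + 0.40 = 2.2.
- At 36 per arm, linear on grade rejects 5% of the time, Mann-Whitney about 9%, chi-square about 60%, and linear on the 0/1 outcome 58%.
- The pattern requires treatment to triple the worst grade, from 10% to 30%.
- If no threshold worsens, a rise in grade 1 from 25% to 50% forces a mean improvement of at least 0.25 grade.

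**5. Successes available to an adjusted model.** 31 × (0.60 + 0.25) = 26.4, and 36 × 0.85 = 30.6, so about 26-31.

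**The case against.** The strongest reply is that little rests on this model. Grade 1 success is tested directly by chi-square, the grade by Mann-Whitney, and the regression is supplementary. That stands, and it sets the severity.

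A reader might infer more: that the adjusted analysis can show nothing while success doubles. The documents do not support that as a general statement. It needs the grade as response, which the article does not say, and it needs treatment to raise both the best and the worst grade, which nothing in the article suggests. On the 0/1 response the coefficient is the risk difference and cannot be zero when success doubles. In the extreme case Mann-Whitney misses the difference nearly as often, so the loss there comes mainly from comparing the whole scale rather than grade 1. A proportional-odds model could be expected to share it.

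The constant-variance point is also weak in practice. With equal arms, the pooled and separate-variance standard errors of a two-group difference coincide, and linear regression on the 0/1 outcome stays close to chi-square in these examples.

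Finally, details may be left to a later plan. That covers the exact response and variance estimator. It does not cover the word linear, which is a stated choice that a later plan would have to overturn.

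**Conclusion.** The mismatch holds. The article names one adjusted model, does not say which form of the outcome it models, and chooses a model family that fits neither the ordinal index nor the relative risk it intends to report.

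The size of the problem is uncertain. With 60% and 25% success at 36 per arm, power of linear regression on grade runs from about 33% (all gain between grades 2 and 1) to about 89-92% (proportional-odds shift), against 86-87% for chi-square. If the response is the 0/1 indicator, power is hardly affected and the fault is one of scale. These figures rest on assumed grade distributions, a two-sided 5% level, 36 evaluable per arm and no covariates in the simulated model.

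It would go too far to say that the trial's main conclusion is at risk, since the direct test of success does not depend on this regression. The point should be fixed; it is not critical.

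**What to change.** In the Data analysis section, state the response of the adjusted model and replace the linear regression with a model that fits it:

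- For grade 1 success: regression on arm, gender and pre-treatment complexity. Modified Poisson with robust standard errors gives the relative risk already promised; logistic regression is an acceptable alternative.
- For the full grade: proportional-odds regression with the same terms, as support.

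Adding centre, or a Firth penalty if cells are sparse, is optional and not needed to cure the mismatch.

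The cost is a change of wording before the final analysis, with no new data. The limitation is that about 26-31 expected successes support only a few covariates, so pre-treatment complexity should enter as one prespecified term.

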### Protocol deviations

▪ All patients failing an appointment will be sent another.▪ Those wishing to withdraw from the trial may do so at any point with no detriment to their continuing treatment. When a patient withdraws from the study the relevant records will be taken at the point of withdrawal.▪ Appliance breakage—every effort will be made for the patient to be seen by a principal operator. However, in certain circumstances, the patient may be seen by a second investigator.▪ If there are more than four breakages for any one patient, then the patient will be removed from the study and records taken at the final breakage appointment.

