### Interventions

Orthodontic treatment will be provided for the treatment group. The treatment will involve fixed braces for the top teeth with or without expanders to widen the top jaw. The brace technique will be a clinical judgement and will be done in real-world setting. The treatment with a fixed brace can take up to 15 months. This will be followed by alveolar bone graft surgery to repair the cleft palate. The alveolar bone graft surgery will be standardised across all surgeons.

In the control group, no orthodontic treatment will be provided but the patients will have alveolar bone graft surgery.

The trial will be carried out in a real-world setting and the patient will not be prohibited from any other care during the trial.

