### Data collection

Data will be collected at the following points:
▪ T1: At the start of treatment/baseline▪ T2: 9 months from baseline▪ T3: Pre alveolar bone graft▪ T4: 3 months post alveolar bone graft▪ T5: 6 months post alveolar bone graft

Records, i.e., study models, intra-oral and extra-oral photographs and a oblique occlusal radiograph will be taken at each time point. A CBCT will be taken at T5 stage.

In addition, the following data will be collected from patients’ notes:
Number of attendances, including failed and cancelled appointmentsOverall treatment durationFrequency of appliance breakages, if anyAny other emergencies

Patients will be required to fill in the Quality of Life questionnaires (CPQ_8-10_) which will inform us how the appliances will affect them as part of the qualitative assessment. The CPQ_8-10_ is a validated questionnaire and has been used in other orthodontic trials.

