### Ancillary and post-trial care

This will be in accordance with the Indian Council of Medical research guidelines.

insurance would be covering all patients participating in the trial for trial-related harms.

The study is a real-world study and is carried out as we would do for patients routinely seen in clinical care. The care for these patients post trial will continue as it would for patients seen routinely in the clinic.

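### A child who withdraws before the graft has no primary outcome, because the protocol provides for records only at the point of withdrawal

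*Protocol article*

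**What the plan says.** Protocol article, Protocol deviations: families may leave at any time without harm to their care, and "When a patient withdraws from the study the relevant records will be taken at the point of withdrawal".

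Outcome measures and Data collection: the primary outcome is success of the bone graft, read from CBCT and the oblique occlusal film. The visits after surgery are T4 (3 months) and T5 (6 months), and "A CBCT will be taken at T5 stage".

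Interventions: in the orthodontic arm, "The treatment with a fixed brace can take up to 15 months". The Rationale gives a range of 6 to 15 months. Controls go to the graft without orthodontics, and the time from randomisation to their surgery is not stated.

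Outcome measures also lists refusal to wear the appliance as a reason to record a patient as non-compliant. Sample size estimation recruits 72 instead of 62 to allow for 10% non-compliance.

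Data analysis: the primary analysis is by intention to treat, and "the results of all subjects will be accounted for, regardless of the outcome of the treatment".

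**The concern.** Records taken before surgery show an ungrafted cleft and hold no information on graft success. If the withdrawal sentence is followed as written, every family that leaves before surgery becomes a missing primary outcome. This undercuts the intention-to-treat aim. The analysis plan cannot repair it, because an analysis can model or bound a missing grade but cannot recover an image that nobody asked to use.

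The article also leaves open what happens to a child who stops the appliance but whose family has not withdrawn. That child is labelled non-compliant, but is not said to remain for T3 to T5. If such children drift out of follow-up, loss becomes linked to tolerance of the treatment under test, and the children with T5 records no longer represent the randomised groups. Attendance and duration data drawn from the notes, which bear on burden and cost, would be cut short in the same way.

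**Working it through.** **1. The plan's own figure.** Sample size estimation states: "With a 5% significance level and 80% power, it is calculated that 31 subjects per group, 62 in total are required for the study". The inputs are "it is estimated that 60% of the treated will have a successful outcome" and "It is estimated that only 25% of the untreated group will have a successful outcome". With a two-sided test (assumed, since sidedness is not stated), pooled variance and no continuity correction, the mean proportion is (0.60 + 0.25)/2 = 0.425:

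n = [1.960·√(2·0.425·0.575) + 0.842·√(0.60·0.40 + 0.25·0.75)]² / 0.35² = (1.370 + 0.550)² / 0.1225 ≈ 30.1, rounded up to 31 per group.

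This reproduces. Inflation by 1/0.9 gives 31/0.9 = 34.4, so 35 per group or 70 in all. The stated 72 implies an allowance of 1 − 62/72 = 13.9%. Dividing by 0.9 is the arithmetic for subjects with no outcome. Under intention to treat, non-compliers keep their outcome and stay in the count.

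**2. Loss before T5.** The documents give no withdrawal rate, so a constant monthly rate r is assumed, with loss = 1 − (1 − r)^m over m months from randomisation to T5. The orthodontic arm has 6 to 15 months before surgery plus 6 after. For controls, two waits are shown: none, and 9 months. The second is included because Data collection lists T2 at 9 months from baseline, ahead of the pre-graft visit, without separating the arms.

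| Pathway | m | r = 0.5% | r = 1% | r = 2% |
|---|---|---|---|---|
| Orthodontic, 15 + 6 | 21 | 10.0% | 19.0% | 34.6% |
| Orthodontic, 6 + 6 | 12 | 5.8% | 11.4% | 21.5% |
| Control, 0 + 6 | 6 | 3.0% | 5.9% | 11.4% |
| Control, 9 + 6 | 15 | 7.2% | 14.0% | 26.1% |

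At 1% per month and 36 per arm, this is about 4 to 7 orthodontic children (36 × 0.114 to 36 × 0.190) and 2 to 5 controls (36 × 0.059 to 36 × 0.140). The difference runs from 19.0 − 5.9 = 13.1 points more loss in the orthodontic arm to 14.0 − 11.4 = 2.6 points more in controls.

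**3. Share leaving before surgery, at 1% per month.** Orthodontic, 15 months: (1 − 0.99^15)/(1 − 0.99^21) = 14.0/19.0 = 74%. Orthodontic, 6 months: 5.9/11.4 = 52%. Control, 9-month wait: (1 − 0.99^9)/(1 − 0.99^15) = 8.6/14.0 = 62%. Control, no wait: nearly all leave after surgery.

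**4. Consequence.** Power with 36 per arm and no loss is 86.8%. It is 82.4% with 10% lost in each arm (32 and 32), 81.7% with 20% lost from orthodontics and 5% from control (29 and 34), and 78.5% with 30% and 5% (25 and 34).

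For bias, suppose 20% of the orthodontic arm is lost and its true success is 60%. The observed rate is (0.60 − 0.20·q)/0.80, where q is the success rate the lost children would have had: 75% if q = 0, 69% if q = 0.25, 60% if q = 0.60 and 50% if q = 1. The direction depends wholly on q, on which the documents are silent.

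**The case against.** Taking exit records when a family leaves a study is ordinary practice and respects its rights. The sentence does not forbid later retrieval with permission. The article condenses a fuller protocol, and consent wording may cover routine records. Appliance refusal has its own category, separate from withdrawal, and intention to treat implies that such children are kept. Accounting for all subjects can be met by reporting withdrawals, and the handling of missing grades belongs to the analysis plan.

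Much of this stands. Refusing the brace is not the same as withdrawing, so a reader who infers that a family tired of the brace must leave the trial goes beyond the text. Missing-data methods are not part of this point. But the withdrawal rule is stated, not merely omitted. No section says that non-compliant children stay for T3 to T5, and the sample-size allowance treats them as lost.

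A reader might also infer that withdrawals will usually precede the graft and be more frequent in the orthodontic arm. The documents do not show this: 15 months is a maximum, the control wait is not given, T2 is not specific to an arm, and there are no withdrawal rates. Nor do they support a spurious gain of a given size for orthodontics, which would need invented success rates among the lost children.

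Finally, "The care for these patients post trial will continue as it would for patients seen routinely in the clinic" concerns care, not imaging. It does not establish that a routine film will exist near 6 months.

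**Conclusion.** The point holds in a limited form. As written, the rule leaves a child who withdraws before surgery without the primary outcome, and the article does not secure T3 to T5 records for children who stop or refuse the appliance. Both weaken the planned intention-to-treat analysis, and both have to be settled before data collection.

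Greater loss in the orthodontic arm is plausible if controls are operated on promptly, but it is not established. The percentages above are illustrations under an assumed constant rate, equal in both arms. Power is little affected within most of the range shown. The exposure is to bias of unknown size and sign. This merits a change to the protocol but does not call the design into question.

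**What to change.** Replace the withdrawal sentence in Protocol deviations with two levels and one safeguard:

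1. A child who stops or declines the allocated treatment, or is recorded as non-compliant, remains in follow-up and has T3, T4 and T5 records as scheduled.
2. A family that leaves trial visits has records taken then and, unless it refuses, is asked for permission to use the notes and any post-graft radiograph obtained in continuing care, taking the one nearest 6 months after surgery.
3. Records taken before the graft are never used as the primary outcome.

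The breakage-removal rule in the same section also ends with records at that visit. It should be reconciled with item 1 as regards follow-up. Nothing here alters treatment.

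The cost is protocol and consent wording and some retrieval work. Some children will have no film, a film outside the 6-month window, or no CBCT, so the gap shrinks but does not close. Loss by arm and a sensitivity analysis for missing grades can be left to the analysis plan.

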### Outcome measures

The primary outcome will be:
Success of alveolar bone graft assessed from CBCT and oblique occlusal (Kindelan method)

The secondary outcome measures will be:
Quality of the dento-occlusal outcome measured on study models using 10-year-old index scoresQualitative assessment using the validated quality of life questionnairesBreakagesQuality-adjusted cost analysis

The operator will record a patient as non-compliant if:
Subject refuses to wear the applianceBreakage of appliance for more than 3 timesMeasurement indicates a lack of clinical progress after 9 months of appliance wear

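### Removing children with repeated appliance breakages from the study conflicts with the intention-to-treat analysis and causes a loss of graft outcomes that falls essentially on the orthodontic arm

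*Protocol article*

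**What the plan says.** All references are to the protocol article.

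- **Protocol deviations:** "If there are more than four breakages for any one patient, then the patient will be removed from the study", with "records taken at the final breakage appointment". Voluntary withdrawal is a separate item in the same list.
- **Interventions:** for the orthodontic arm, "The treatment will involve fixed braces for the top teeth with or without expanders to widen the top jaw"; the graft comes after this phase. For the other arm, "In the control group, no orthodontic treatment will be provided but the patients will have alveolar bone graft surgery".
- **Outcome measures:** the primary outcome is success of the graft. A child with more than three breakages is among those the operator records as non-compliant; no removal is attached to that flag.
- **Data collection:** records are scheduled before the graft (T3) and at 3 and 6 months after it (T4, T5).
- **Data analysis:** "The primary analysis will be on an intention-to-treat principle; the results of all subjects will be accounted for, regardless of the outcome of the treatment".

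Nothing in the article says that a removed child is still followed to T5.

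**The concern.** Intention-to-treat needs an outcome, or at least an attempt to obtain one, for every randomised child. The removal rule ends data collection before the primary outcome can exist. Its trigger is tied to the allocated treatment, because controls have no trial appliance to break. The investigators impose the loss, so it is avoidable, unlike a family's own decision to withdraw.

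The protocol itself treats repeated breakage as a sign of non-compliance. It is therefore reasonable to expect that removed children might differ in prognosis from those who stay. If they would have done worse, leaving them out flatters the orthodontic arm. If the film from the last breakage visit, which shows an ungrafted cleft, were scored as the outcome, they would count as failures and the orthodontic arm would be penalised. The trial asks whether pre-graft orthodontics is needed at all, so a distortion in either direction touches its main conclusion.

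**Working it through.** **1. The sections side by side.** Braces are worn before the graft; the rule removes a child for breaking the brace and closes the record at that visit; the primary outcome is read after the graft. For a child removed in the brace phase, the records hold no T4 or T5 film, yet the primary analysis is to account for every subject.

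**2. The plan's own figure.** Inputs from Sample size estimation: success 60% treated and 25% untreated, 5% significance, 80% power. With a two-sided test and pooled variance, mean proportion 0.425:

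n = [1.96 × √(2 × 0.425 × 0.575) + 0.842 × √(0.60 × 0.40 + 0.25 × 0.75)]² / 0.35² = 30.1, rounded up to 31 per group.

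This reproduces the stated 31. The 72 to be recruited at 1:1 give 36 per arm, which is used below. The sample size is not in dispute.

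**3. Assumptions.** The documents give no breakage rate. Let r be the share of the orthodontic arm removed: 5%, 10% or 20%, about 2, 4 or 7 of 36. Let q be the success rate that removed children would have had if followed; 25%, the untreated rate, is used for illustration.

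**4. Removed children excluded.** The observed orthodontic rate is (0.60 − r × q)/(1 − r). With q = 0.25:

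- r = 5%: 0.5875/0.95 = 61.8%
- r = 10%: 0.575/0.90 = 63.9%
- r = 20%: 0.55/0.80 = 68.8%

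With q = 0.60 and r = 10%: (0.60 − 0.06)/0.90 = 60%, so no bias.

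**5. Removed children scored as failures, same q = 0.25.** The observed orthodontic rate is 0.60 − r × 0.25, against 25% in controls. Power is exact, for the two-sided uncorrected chi-square test at 36 per arm:

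| Removed | Orthodontic rate | Power |
|---|---|---|
| 0% | 60.0% | 86% |
| 5% | 58.75% | 84% |
| 10% | 57.5% | 81% |
| 20% | 55.0% | 75% |

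**6. No true difference, removed children excluded.** Take 40% success in both arms and 10% among those removed. The observed orthodontic rate is (0.40 − r × 0.10)/(1 − r):

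- r = 10%: 0.39/0.90 = 43.3%. With 32 against 36 analysed, the nominal 5% test rejects 5.6% of the time, compared with 4.9% when nobody is removed.
- r = 20%: 0.38/0.80 = 47.5%. With 29 against 36 analysed, it rejects about 10% of the time.

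**The case against.** The case for leaving the rule alone is that few children may exceed four breakages, that the handling of missing outcomes belongs to an analysis plan not shown here, and that the article does not say removed children are dropped or that the breakage film is scored. All of this is fair, and it limits what can be said about size. At 10% removed, the illustrations move the results only modestly. Ten per cent may itself be high, because the protocol's non-compliance definition also covers refusal to wear the appliance and lack of progress, and only some of those children would exceed four breakages. What does not stand is the deferral to a later plan: it can choose an imputation, but it cannot supply a film that the protocol stops collecting.

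Several stronger readings are tempting and are not supported:

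- **Bias is certain.** It is zero if removed children would have done as well as the rest. Neither its size nor its direction can be computed from the documents.
- **Removal is impossible in controls.** Other care is not prohibited, so a control child with an appliance cannot be strictly ruled out. The loss falls essentially, not provably only, on one arm.
- **Power collapses under failure scoring.** Power of 72% at 10% removed and 54% at 20% follows only if removed children would otherwise have succeeded at the full 60% (0.60 × 0.90 = 54%; 0.60 × 0.80 = 48%). That cannot be combined with the 25% used for exclusion.
- **The two breakage thresholds contradict each other.** More than three leads to a flag and more than four to removal. These are different consequences and can coexist.
- **The sample-size allowance shows that non-compliant children leave the analysis.** The sentence "To allow for a 10% non-compliance rate, 72 subjects will be recruited into the study" does not say so; it is equally compatible with ordinary attrition.

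**Conclusion.** The removal rule and the intention-to-treat statement conflict as written. For any child removed during the brace phase, the protocol cannot deliver the primary analysis it promises. The loss is avoidable, falls essentially on the orthodontic arm and may be informative.

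That conclusion rests on the text alone. The size does not: it depends on an assumed removal share of 5-20% and an assumed success rate among removed children. On those assumptions the upward shift in the orthodontic success rate runs from 1.8 to 8.8 percentage points under exclusion. Under failure scoring, power stays above the planned 80% at 10% removed and falls below it at 20%. In the null illustration, the test's error rate is little affected at 10% removed and roughly doubles at 20%. The point deserves correction because the conflict is plain and outcomes already lost cannot be restored, not because a large bias has been shown.

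**What to change.** Reconcile Protocol deviations with Data analysis by separating any decision about the appliance from participation in the study. In place of removal, state that:

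- repeated breakage is recorded as an adherence event, whatever is decided clinically about the appliance;
- the child stays in follow-up, and the scheduled T3 to T5 records are collected unless the family withdraws;
- the child is analysed in the randomised arm.

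Use the non-compliance flag in Outcome measures only for description or for a supportive analysis labelled as such. No breakage threshold or clinical rule is proposed here.

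The cost is protocol wording; the T3 to T5 records are already scheduled for participants. The small downside is some dilution of the effect estimate from keeping poorly adherent children, which is inherent in the intention-to-treat question the protocol has chosen. The change should be made early, since it cannot recover outcomes already missed.
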